**Fig. 2 Fig2:**
[figure not shown]
SPIRIT figure

### Phase 1—feasibility trial

#### Recruitment

Trauma care in England is delivered through specialist centres [29]. Indeed, patients will be recruited from major trauma centres in London. Direct members of the care team will screen patients using inclusion and exclusion criteria and provide eligible patients with an information sheet and consent form.

#### Eligibility criteria

Inclusion criteria consists of patients over the age of 18 with a non-penetrating head injury, able to provide informed consent (or with a consultee willing to provide advice), inpatient on a trauma or outlying ward and a sufficient grasp of English to complete outcome measures. Patients will be excluded if they have a current history of substance abuse, are medically unstable, are pregnant, have vascular or orthopaedic injuries precluding neck extension, have active psychiatric disease or a history of psychotic disease, have a Glasgow Coma Score less than 14, or have a current prescription of phenytoin.

#### Assessment

Eligible patients who consent to take part in the study will be assessed by a ward therapist for BPPV using a Dix Hallpike manoeuvre (Fig. 3), which is the gold standard diagnostic test [25]. Therapists (occupational therapists and physiotherapists) will be trained to undertake such manoeuvres prior to the study commencing.

**Fig. 3 Fig3:**
[figure not shown]
Schematic representation of the Dix Hallpike, the diagnostic test for BPPV. Patients lie supine with their head rotated 45° and extended 20°. Figure kindly provided by [name], April 2020

#### Randomisation

Those diagnosed with BPPV will be randomised to one of three intervention arms (Fig. 4). Patients testing negative for BPPV will not take further part in the trial. Randomisation will occur through an online randomisation platform (Sealed Envelope) which uses sequential treatment assignment. Minimisation criteria will be used to ensure groups are balanced. Trial participants and outcome assessors will be blinded to group allocation; however, due to the physical nature of the interventions, blinding of the therapists delivering the intervention will not be possible.

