**Method:**

A multi-centre randomised mixed methods feasibility study design was employed. We aim to recruit approximately 75 acute TBI patients across a range of clinical severities, from three major trauma centres in London. Patients will be randomised to one of three treatment arms: (1) therapist-led manoeuvres, (2) patient-led exercises and (3) advice. Participants will be re-assessed by blinded outcome assessors at 4 and 12 weeks. Acceptability of the intervention will be obtained by patient interviews at the end of their treatment and therapist interviews at the end of the study. Primary outcomes relate to feasibility parameters including recruitment and retention rates, adverse events and intervention fidelity. We will also aim to provide a more accurate estimate of the prevalence of BPPV in TBI cases on the trauma ward.

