#### Interventions

Participants will be randomly allocated to one of three arms: (1) therapist-led repositioning manoeuvres, (2) patient-led exercises, or (3) advice.
*Therapist-led repositioning manoeuvres*

Repositioning manoeuvres are physical movements of the head and body typically used to treat idiopathic or traumatic BPPV [25]. Ward therapists will be taught to perform repositioning manoeuvres as per clinical guidelines [25]. Those diagnosed with BPPV affecting both left and right sides will be treated with the most symptomatic side first (or the side with the most intense nystagmus if the participant is not symptomatic). A repeat diagnostic test will be subsequently performed to determine the success of the intervention. The number of manoeuvres required for resolution of BPPV will vary between participants. If acceptable, the therapist will continue completing manoeuvres, up to a maximum of three manoeuvres per session, and a maximum of three sessions (over subsequent days where applicable). Participant discomfort, nausea, or vomiting would be indications to cease treatment. Any adverse events or reasons to stop the intervention will be recorded.
2.*Patient-led exercises*

Patient-led or Brandt-Daroff exercises are a form of physical self-treatment involving repeated movements of the head and trunk prescribed by clinicians as an alternative to, or in tandem with, repositioning manoeuvres. The National Institute of Clinical Evidence suggest Brandt-Daroff exercises as a treatment option for idiopathic BPPV [30], although their effectiveness is unknown post TBI.

Ward therapists will teach participants and carers (where required) the Brandt-Daroff exercises. A repeat diagnostic test will be completed. Following treatment, participants will be instructed to complete the exercises twice per day for 2 weeks, using a standardised, written exercise sheet. Participants will be asked to complete a home diary to record their adherence with the exercises.
3.*Advice*

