Ward therapists will provide participants with verbal and written advice. This will comprise ensuring adequate fluid intake, taking precautions when mobilising independently on the ward or at home and trying to ensure normal head and body movement patterns. Advice will be provided in the course of the participant’s hospital stay, during a scheduled therapy session. Such advice is based on evidence suggesting dizzy patients who avoid head movements may be prone to motion sensitivity, which can delay recovery and contribute to long-lasting subjective dizziness and imbalance [31, 32]. A brief further session, repeating the advice will be provided prior to participant’s discharge. Following the last treatment session, a repeat diagnostic test will be performed to ascertain the presence of BPPV.

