#### Outcome measures

Baseline demographic data will be recorded including age, gender, factors relating to the head injury, functional status, falls and past medical history. Primary outcome measures relate to feasibility objectives: number of eligible patients, time taken to fulfil recruitment target, trial dropout rates, variability in intervention fidelity, proportion of outcome measures completed and any adverse events noted throughout the trial.

Secondary outcomes will be collected at three timepoints:
Timepoint 0—during hospital stay, following consent, randomisation and prior to treatmentTimepoint 1—at 4 weeks following treatmentTimepoint 2—at 12 weeks following treatment

Secondary outcomes comprise the diagnostic test for BPPV (Dix Hallpike manoeuvre) to explore the frequency and recurrence rate of BPPV, in addition to a range of self-reported measures explored below.

Self-reported disability pertaining to dizziness will be evaluated using the Dizziness Handicap Inventory (DHI), a 25-item questionnaire with high test re-test reliability and low error of measurement score [34]. Dizziness frequency and severity will be examined by the UCLA Dizziness questionnaire [35]. The Activities-specific Balance Confidence scale will explore subjective balance confidence by asking participants to rate how balanced they feel completing sixteen different day to day tasks. Previous research in older adults has demonstrated scores less than 67% indicate a high risk of falling [36].

Cognitive function will be screened using the Montreal Cognitive Assessment (MoCA), a standardised test of visuo-spatial and executive function, naming, memory, attention, language, abstraction and orientation, routinely used in clinical settings [37]. Health outcome will be measured using the EQ-5D, a widely used tool consisting of five items regarding mobility, usual care activities, self-care, anxiety and depression and pain. Scores will also be used for economic evaluation during a definitive trial [38]. Anxiety and depression will be screened using the Hospital Anxiety and Depression scale (HADS). Participants respond by rating each question on a 4-point scale, with higher scores indicating increased levels of anxiety and/or depression [39].

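### The protocol says participants are blinded to allocation, but three openly different arms with no sham rule this out; participant-rated outcomes should be treated as unblinded

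*Protocol article*

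**What the plan says.** The Randomisation section states "Trial participants and outcome assessors will be blinded to group allocation". The same sentence then excepts the therapists: "due to the physical nature of the interventions, blinding of the therapists delivering the intervention will not be possible". The Abstract (Method) makes a narrower claim: "Participants will be re-assessed by blinded outcome assessors at 4 and 12 weeks". It does not mention blinding of participants.

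The Interventions section lists the arms as "1) therapist-led repositioning manoeuvres, (2) patient-led exercises, or (3) advice". For the exercise arm, "participants will be instructed to complete the exercises twice per day for 2 weeks, using a standardised, written exercise sheet", and "Participants will be asked to complete a home diary to record their adherence with the exercises". For the comparator, "Ward therapists will provide participants with verbal and written advice".

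Under Outcome measures, the secondary outcomes comprise the Dix Hallpike test "in addition to a range of self-reported measures explored below", followed by cognitive, functional, work and balance measures. The Aim and objectives and Sample size sections say that secondary outcomes will provide effect sizes and inform the sample size of a future randomised trial.

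**The concern.** The blinding statement is an affirmative claim about the design, without qualification. It is therefore not a detail that a condensed article has merely left to the full protocol. A person who is moved through repositioning manoeuvres, or who does exercises daily and logs them, or who is only advised, knows which of the three treatments they had.

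What is at stake is how the self-rated outcomes are read. When the participant does the rating, the participant is in effect the assessor, and a blinded member of staff who hands over the questionnaire does not blind the answer. If the statement stands, between-arm differences on these scales could be carried into the planning of the definitive trial on a masking assumption that this design cannot meet.

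**Working it through.** No figure in the protocol depends on participant blinding, so there is nothing to reproduce. The check sets the sections side by side.

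1. **What is claimed.** Randomisation: participants and outcome assessors are blinded to group allocation. The claim concerns allocation itself, not the hypothesis or which arm is the comparator.

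2. **Whether the arms can be told apart by the recipient.**
   - Arm 1: physical manoeuvres by a therapist, up to three per session and up to three sessions.
   - Arm 2: exercises that the participant performs twice daily for 2 weeks, with a written sheet and a diary.
   - Arm 3: verbal and written advice, repeated before discharge.

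   No sham manoeuvre, dummy exercise or partial disclosure is described. The arms differ in what the participant does and feels.

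3. **Whether the protocol's own reasoning covers participants.** Therapists are said to be unblindable because the interventions are physical. That reason applies equally to the person who receives or performs them.

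4. **Whether other sections agree.** The Abstract claims blinded outcome assessors only. In Phase 2, about 18 participants, 6 per arm, are to be interviewed on topics that include the intervention they had, which presupposes that they know what it was.

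5. **Which outcomes are affected.**
   - Participant-rated (six): DHI, UCLA Dizziness questionnaire, ABC, EQ-5D, HADS, quality of life after brain injury.
   - Tested or assessor-administered (five): Dix Hallpike, MoCA, extended Glasgow outcome by structured interview, mCTSIB, mDGI.
   - Mixed: the Work Quality Index.

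   Timepoint 0 falls after randomisation but before treatment, so participants may not yet know their arm then. The problem applies at 4 and 12 weeks, which are the between-arm comparisons.

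6. **What depends on them.** The primary outcomes are feasibility measures. The progression criteria are eligibility, consent and dropout. The two regressions have return to work and BPPV at 3 months as outcomes, and DHI enters only as a predictor. The sample of 75 (3 × 25) rests on a published recommendation, not on a power calculation. What does depend on the self-ratings is the use of secondary outcomes for effect sizes and future sample size.

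**The case against.** The strongest reply has four parts.

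- **Knowing the treatment is not knowing the hypothesis.** All three arms are called intervention arms in the Randomisation section, and all include therapist contact and a repeat diagnostic test. The information sheet is not shown, so participants may not know which arm is favoured. This stands as a limit on what can be said about bias. It does not rescue the sentence, which speaks of group allocation.

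- **Nothing labels the questionnaires as blinded.** A reader might infer that the self-reports are being presented as double-blind. The documents do not support that: the Outcome measures section attaches no blinding label to any scale, the term double-blind does not appear, and the therapists are openly unblinded. This stands.

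- **The consequence is limited.** The primary outcomes and progression criteria contain no self-rated scale, and between-arm estimates will be imprecise anyway. With 25 per arm, the standard error of a standardised difference is about √(2/25) = 0.28, a 95% interval of ±1.96 × 0.28 = ±0.55 SD. At the tolerated 40% dropout (25 × 0.6 = 15 per arm) it is 1.96 × √(2/15) = ±0.72 SD. This stands as to scale, although imprecision does not remove a bias.

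- **A definitive trial of the same arms would also be open to participants,** so its observed effects would carry similar expectation effects. This is partly right, and it is a reason to describe the masking correctly now, so that the next trial is planned knowingly.

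**Conclusion.** The statement that participants are blinded to allocation is wrong as written and is at odds with the Interventions section; the Abstract claims only blinded assessors. The six participant-rated outcomes are unblinded at 4 and 12 weeks in every arm.

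The conclusion rests on one assumption, that no sham or masking exists beyond what the article describes. If something narrower was meant, such as withholding the hypothesis, the sentence still needs to say so.

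Two stronger readings are tempting and are not supported. A reader might infer a bias of a particular size against the advice arm, but the documents give neither a size nor a direction. A reader might also infer that assessor blinding fails, but nothing in the article disproves it for the Dix Hallpike or the balance tests. Nor does the point require a lead efficacy outcome to be named in a feasibility trial. The feasibility primary outcomes, the progression criteria and the sample of 75 are unaffected. The point is a correction to a stated design property, with a real but bounded effect on how secondary effect sizes are read.

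**What to change.** - In the Randomisation section, state that outcome assessors are blinded and that participants and treating therapists are not; or state exactly what is withheld from participants, for example the hypothesis. Make the Abstract and the Randomisation section agree.
- Treat DHI, UCLA, ABC, EQ-5D, HADS and quality of life after brain injury as unblinded when between-arm effect sizes are reported or used to plan the future trial. Show them alongside the assessor-blinded measures (Dix Hallpike, mCTSIB, mDGI).
- Optionally, ask participants not to reveal their treatment to assessors, and record assessors' guesses of allocation at 4 and 12 weeks. This would also tell the next trial how well assessor blinding held.

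The essential change is wording and labelling. The optional step adds one item to the follow-up form. The downside is that the stated blinding becomes less favourable.

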**Fig. 4 Fig4:**
[figure not shown]
Simplified study flow chart

#### Interventions

Participants will be randomly allocated to one of three arms: (1) therapist-led repositioning manoeuvres, (2) patient-led exercises, or (3) advice.
*Therapist-led repositioning manoeuvres*

Repositioning manoeuvres are physical movements of the head and body typically used to treat idiopathic or traumatic BPPV [25]. Ward therapists will be taught to perform repositioning manoeuvres as per clinical guidelines [25]. Those diagnosed with BPPV affecting both left and right sides will be treated with the most symptomatic side first (or the side with the most intense nystagmus if the participant is not symptomatic). A repeat diagnostic test will be subsequently performed to determine the success of the intervention. The number of manoeuvres required for resolution of BPPV will vary between participants. If acceptable, the therapist will continue completing manoeuvres, up to a maximum of three manoeuvres per session, and a maximum of three sessions (over subsequent days where applicable). Participant discomfort, nausea, or vomiting would be indications to cease treatment. Any adverse events or reasons to stop the intervention will be recorded.
2.*Patient-led exercises*

Patient-led or Brandt-Daroff exercises are a form of physical self-treatment involving repeated movements of the head and trunk prescribed by clinicians as an alternative to, or in tandem with, repositioning manoeuvres. The National Institute of Clinical Evidence suggest Brandt-Daroff exercises as a treatment option for idiopathic BPPV [30], although their effectiveness is unknown post TBI.

Ward therapists will teach participants and carers (where required) the Brandt-Daroff exercises. A repeat diagnostic test will be completed. Following treatment, participants will be instructed to complete the exercises twice per day for 2 weeks, using a standardised, written exercise sheet. Participants will be asked to complete a home diary to record their adherence with the exercises.
3.*Advice*

Ward therapists will provide participants with verbal and written advice. This will comprise ensuring adequate fluid intake, taking precautions when mobilising independently on the ward or at home and trying to ensure normal head and body movement patterns. Advice will be provided in the course of the participant’s hospital stay, during a scheduled therapy session. Such advice is based on evidence suggesting dizzy patients who avoid head movements may be prone to motion sensitivity, which can delay recovery and contribute to long-lasting subjective dizziness and imbalance [31, 32]. A brief further session, repeating the advice will be provided prior to participant’s discharge. Following the last treatment session, a repeat diagnostic test will be performed to ascertain the presence of BPPV.

#### Intervention fidelity

Fidelity monitoring is an important part of any rehabilitation research intervention, enabling investigators to differentiate between comparator and experimental interventions and ensuring any procedures are carried out as defined in the protocol or guidelines [33]. In this study, video will be used to record therapists performing the interventions. Independent raters will observe and evaluate approximately 10% of therapy sessions, using a competency record sheet. This approach has been previously utilised in studies evaluating treatment fidelity [33].

#### Outcome measures

Baseline demographic data will be recorded including age, gender, factors relating to the head injury, functional status, falls and past medical history. Primary outcome measures relate to feasibility objectives: number of eligible patients, time taken to fulfil recruitment target, trial dropout rates, variability in intervention fidelity, proportion of outcome measures completed and any adverse events noted throughout the trial.

Secondary outcomes will be collected at three timepoints:
Timepoint 0—during hospital stay, following consent, randomisation and prior to treatmentTimepoint 1—at 4 weeks following treatmentTimepoint 2—at 12 weeks following treatment

Secondary outcomes comprise the diagnostic test for BPPV (Dix Hallpike manoeuvre) to explore the frequency and recurrence rate of BPPV, in addition to a range of self-reported measures explored below.

Self-reported disability pertaining to dizziness will be evaluated using the Dizziness Handicap Inventory (DHI), a 25-item questionnaire with high test re-test reliability and low error of measurement score [34]. Dizziness frequency and severity will be examined by the UCLA Dizziness questionnaire [35]. The Activities-specific Balance Confidence scale will explore subjective balance confidence by asking participants to rate how balanced they feel completing sixteen different day to day tasks. Previous research in older adults has demonstrated scores less than 67% indicate a high risk of falling [36].

Cognitive function will be screened using the Montreal Cognitive Assessment (MoCA), a standardised test of visuo-spatial and executive function, naming, memory, attention, language, abstraction and orientation, routinely used in clinical settings [37]. Health outcome will be measured using the EQ-5D, a widely used tool consisting of five items regarding mobility, usual care activities, self-care, anxiety and depression and pain. Scores will also be used for economic evaluation during a definitive trial [38]. Anxiety and depression will be screened using the Hospital Anxiety and Depression scale (HADS). Participants respond by rating each question on a 4-point scale, with higher scores indicating increased levels of anxiety and/or depression [39].

Three further questionnaires will be used at timepoints 1 and 2 to explore functional recovery, return to work and quality of life. The Glasgow Coma Outcome Score is a tool extensively used in phase III trials as a primary measure of recovery following TBI [40]. The extended version of the measure, via structured interview, splits the latter three of five categories (death, vegetative state, severe disability, moderate disability and good recovery) into upper and lower domains to improve sensitivity. Return to work following TBI will be measured using the Work Quality Index—a measure of both work status and stability [41]. Participants are divided into four working status categories, and then subsequently into four working stability domains, giving a composite measure of work quality. The Quality of Life after Brain Injury measure was specifically developed for the TBI population and has been validated through two large multi-centre studies [42]. Participants rate their quality of life on 37 items in six scales assessing areas of cognition, self, daily life and autonomy, social relationships and their emotions and physical problems.

Objective balance outcomes (modified clinical test of sensory integration in balance (mCTSIB) and modified Dynamic Gait Index (mDGI)) will be measured at all three time points. The mCTSIB evaluates how participants are able to use sensory inputs during static balance in four conditions; feet together and eyes open or closed on a hard or soft surface for 30 s. This test has demonstrated excellent reliability and validity in those with vestibular disorders [43]. The mDGI comprises eight dynamic walking tasks. Raters evaluate gait pattern, level of assistance and time taken to complete the task. The psychometric properties of this measure have been investigated in several neurological populations including TBI [44, 45].

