#### Planned data analysis

Results will be reported descriptively to chart demographic and observational data. Participant recruitment/retention data will be reported using pilot and feasibility CONSORT guidelines [52]. An estimate of the prevalence of BPPV in acute TBI will be reported with 95% confidence intervals. The analysis will be undertaken on an ‘intention to treat’ basis, i.e. analysis will include all patients at the end of the study, whether or not they complete the intervention. We will assess the predictors of (i) return to work and (ii) BPPV at 3 months via a binary multiple logistic regression with predictors: DHI score, intervention group, duration of post traumatic amnesia and the presence of skull fracture. Our projected sample size of 75 patients should be sufficient to test these regression models given that each one has four variables. As there are two regression models, which both use the same predictor variables, the alpha will be adjusted (*α* = .025) based on the Bonferroni correction. We do not expect to demonstrate significant results from this data; rather, it will be used to calculate effect sizes for future prospective treatment studies.

Qualitative data will be transcribed verbatim and analysed using a Framework approach [53, 54]. This type of analysis uses a series of interconnected stages which enables the researcher to move back and forth across the data until a coherent account emerges. Following familiarisation with the transcripts, a framework is developed according to key issues or themes, into which data is then indexed. Data is then summarised by category and charted using the final coding index. Finally, key characteristics and differences between data are identified, allowing the generation of concepts, connections and relationships.

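### Timepoint 0 is scheduled after randomisation, so no pre-randomisation score is planned for the baseline questionnaires and balance tests, and a patient can be randomised with no baseline

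*Protocol article*

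**What the plan says.** Under Outcome measures, the protocol article states that "Secondary outcomes will be collected at three timepoints". It defines the first, timepoint 0, as "during hospital stay, following consent, randomisation and prior to" treatment. The measures listed for this schedule are the Dix Hallpike, the DHI, the UCLA Dizziness questionnaire, the Activities-specific Balance Confidence (ABC) scale, the MoCA, the EQ-5D and the HADS. The two balance tests, mCTSIB and mDGI, "will be measured at all three time points". Three further instruments (extended Glasgow outcome, work quality, quality of life after brain injury) start at timepoint 1 and are not affected.

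Under Assessment, consenting patients are tested with a Dix Hallpike by a ward therapist. Under Randomisation, "Those diagnosed with BPPV will be randomised to one of three intervention arms", and patients who test negative leave the trial.

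On blinding, the Randomisation section says "Trial participants and outcome assessors will be blinded to group allocation" and adds that the therapists who deliver treatment cannot be blinded. The abstract says "Participants will be re-assessed by blinded outcome assessors at 4 and 12 weeks".

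Under Planned data analysis, both logistic regressions use the "predictors: DHI score, intervention group, duration of post traumatic amnesia and the presence of skull fracture". No timepoint is attached to the DHI score.

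**The concern.** A baseline is best recorded before the allocation exists, because then it cannot be influenced by the arm and every randomised patient has one. The stated order gives up both safeguards.

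First, completeness. The patients are acute inpatients, and the battery has nine parts. Anyone discharged, or too tired to continue, between allocation and the end of that battery is already in the trial without a full baseline.

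Second, the measures include self-report scales and a rater-scored gait test ("Raters evaluate gait pattern, level of assistance and time taken to complete the task"). These are open to influence if the patient or the rater knows the arm.

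What is at stake is the secondary objective of supplying effect sizes for a future trial, and the usefulness of this study as a template. A definitive trial could inherit the same sequence.

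**Working it through.** The point concerns the order of procedures and rests on no stated figure, so there is none to reproduce. The check sets the sections side by side.

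1. **Order.** Assessment gives consent, then Dix Hallpike. Randomisation follows a positive result. Outcome measures puts timepoint 0 after randomisation and before treatment. Read together: consent, Dix Hallpike, randomisation, timepoint 0, treatment.

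2. **Scores planned before randomisation.** For the DHI, UCLA, ABC, MoCA, EQ-5D, HADS, mCTSIB and mDGI (eight measures) the number is 0. Demographic data carry no stated timing, and any item used for minimisation must be known before allocation, so those are outside the point.

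3. **Dix Hallpike.** The diagnostic test must precede randomisation, yet the same test is a timepoint 0 outcome and timepoint 0 follows randomisation. Either the test is done twice before treatment, which no section describes, or the timepoint 0 value is really the diagnostic one and the definition of timepoint 0 is wrong for it. The text does not settle which.

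4. **Who could know the arm at timepoint 0.**
   - Participants and outcome assessors are stated to be blinded, with no restriction to follow-up.
   - No section says who collects timepoint 0.
   - Ward therapists perform the diagnostic test and deliver all three arms, and those delivering treatment are unblinded.
   - The abstract mentions blinded assessors only for the re-assessments.

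   So the text neither shows that the arm is known at timepoint 0 nor rules it out.

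5. **DHI predictor.** Of the three collection points, one follows randomisation and two follow treatment. Read literally, no choice of timepoint yields a pre-randomisation DHI. That the timepoint 0 score is meant is a reasonable inference, but it is not stated.

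6. **Scale of lost baselines (illustration only).** The article gives no rate of missing baselines, so the share m is assumed. The planned total is 3 × 25 = 75. If the regressions use the timepoint 0 DHI and complete cases only, and if missing baseline is unrelated to drop-out d, the usable number is 75 × (1 − d) × (1 − m):

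| Assumed m | d = 0 | d = 0.40 (the ceiling in the progression criteria) |
|---|---|---|
| 0% | 75.0 | 45.0 |
| 5% | 71.2 | 42.8 |
| 10% | 67.5 | 40.5 |
| 20% | 60.0 | 36.0 |

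For example, 75 × 0.60 × 0.90 = 40.5. These counts show scale and are not a forecast.

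**The case against.** The strongest reply is the blinding statement. It covers participants and outcome assessors without limiting itself to follow-up, and the timepoint 0 measures are listed as secondary outcomes. Timepoint 0 also precedes treatment, and the arms become visibly different only when treatment is delivered. No section says that patients learn their arm earlier or that the treating therapist collects the baseline. The abstract's sentence describes re-assessment and does not say that baseline is unblinded. This stands to the extent that bias cannot be asserted: if blinding holds at timepoint 0, it is zero. It does not close the matter, because the assessor at timepoint 0 is not identified.

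A second reply is that the definition of timepoint 0 is condensed wording. It cannot be literally true of the diagnostic Dix Hallpike, and the SPIRIT figure and flow chart, which were not readable in the text used here, may show a different order. That is possible, but it supports correcting the sentence.

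A third reply concerns weight. Feasibility is the primary aim, effect sizes are secondary, and no significant results are expected. Completeness of outcome measures is itself a primary outcome, so missing baselines would be seen and reported. This stands and limits the importance of the point.

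Neither reply to the bias question touches the other half of the point: blinding does not give a baseline to a patient who was randomised and then left.

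**Conclusion.** The point holds in a limited form. As written, eight baseline measures have no planned pre-randomisation score, a patient can be randomised with no baseline, and the definition of timepoint 0 does not fit the test that leads to randomisation. These conclusions follow from the text and depend on no assumption about blinding, only on reading the timepoint 0 definition literally.

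Influence of allocation on the baseline scores is a possible risk of unknown size. It is zero if the stated blinding holds at timepoint 0.

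Three stronger readings might be inferred, and the documents do not support them:

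- **That the effect estimates are biased by some stated amount.** No section shows that anyone assessing or answering at timepoint 0 knows the arm. The planned models are two logistic regressions, so figures in standard deviations for change scores or adjusted means would describe analyses that are not planned.
- **That missing baselines count against the 40% drop-out criterion.** The progression criteria do not define drop-out in that way.
- **That the DHI covariate is contaminated.** Its timepoint is not stated, and a blinded pre-treatment score would serve as a baseline even though it was taken after randomisation.

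The change is worth making because it removes an avoidable weakness at almost no cost. The weakness does not undermine the feasibility aims.

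**What to change.** Make four linked changes:

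1. In Outcome measures, redefine timepoint 0 as after a positive Dix Hallpike and before randomisation.
2. Require the baseline forms to be saved in REDCap before the allocation is requested from the online service.
3. Use the diagnostic Dix Hallpike as the timepoint 0 test.
4. In Planned data analysis, state that the DHI predictor is this pre-randomisation score.

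The SPIRIT figure and flow chart should be checked against the new wording.

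The cost is wording and the order of forms. BPPV status is already known before randomisation, so no additional test is needed. The small downside is that a few patients may complete the baseline and then not be randomised.
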